### Follow-up period (Visit 15)

During the follow-up subjects will be visited at convenience (up to every 2 h). At each visit, the CGM values will be recorded and compared with values obtained as part of routine clinical practice.

### Notes

As the CGM values are available to the attending physicians responsible for perioperative patient care, these data might raise awareness of dysglycaemic events that might have been overlooked. The physicians can treat dysglycaemic events to the best of their knowledge and treatments should be initiated according to local standards once the CGM values have been confirmed by another device. The study protocol does not provide recommendations on how to treat dysglycaemic events.

Complications of central venous cannulisation have been recognised since the technique was first introduced into clinical use. Overall, > 15% of patients undergoing central venous cannulisation experience complications [20]. Although serious acute complications are rare when central venous cannulisation is performed by well-trained, experienced clinicians, infectious complications are relatively common, and the technique may result in significant morbidity and mortality. Considering these complications and their origin, all conceivable measures will be taken to prevent participants from any harm. Nevertheless, the study is not designed to investigate the efficacy or safety of central venous cannulisation. Therefore, central venous cannulisation is not considered a study-specific intervention.

### Statistical methods

The test statistic for testing the null hypothesis $H_{o}:\left|\delta \right|+2\sigma >\lambda$ is calculated as $Z=\frac{\left|\bar{d}\right|\pm 2s_{d}-\lambda }{\sqrt{3/ns_{d}^{2}}}$, where λ=20% for the outcome measure. Its distribution under $\left|\delta \right|+2\sigma =\lambda$ is asymptotically normal. Therefore, the null hypothesis is rejected if *Z* is below the 0.05 quantile of the normal distribution. Descriptive statistics of continuous variables and scores include the number of observations, the mean and standard deviation, the median, minimum, and maximum. Descriptive statistics of categorical variables (nominal or ordinal) include absolute and relative frequencies (n and per cent). The primary outcome measure is the level of agreement in blood glucose levels determined by the CGM and a BGA, assessed 8 h after the initial placement and calibration of the CGM using the relative difference $\bar{d}$, as described above. Bland and Altman plots will be drawn, including the CIs for the mean difference and limits of agreement to show the agreement between the pairs of values [9,21]. Secondary analyses, including the level of agreement between the two devices at each time after placement and calibration of the CGM will be analysed descriptively, while applying the same equivalence bounds used in the primary analysis. A linear mixed model will be developed using time as the fixed factor. Subject and the interaction subject × time will be included as random explanatory variables. The individual values $\bar{d}$ at all times up to 8 h will be included as the response variable. This model will be used to impute missing data. Biometric analysis will be defined in the statistical analysis plan, which must be authorised before the database is opened by the biostatistician, the sponsor, and the principal investigator.

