### Sample size

The agreement between the two devices will be quantified using the approach suggested by Bland and Altman, in which the 95% limits of agreement with 95% CIs will be compared with a prespecified, clinically acceptable relative difference [9] of 20%. The standard error of the 95% limits of agreement is approximately $\mathrm{se}\approx \sqrt{\frac{3s_{d}^{2}}{n}}$, where $s_{d}$ is the standard deviation of the differences between the two devices and n is the sample size (number of paired values the differences are calculated from). The sample size is dependent on the intended width of the CIs. Bland and Altman recommend a sample size of 100, which gives a 95% CI of about ± 0.34$s_{d}$, or about one-sixth of the width of the actual agreement. The power to reject the hypothesis that the prespecified limits of agreement of ± 20% are violated is > 80% if $\frac{\delta +\;2\sigma -\;\lambda }{\sqrt{\frac{3\sigma^{2}}{n}}}<-\;2.486$, where λ is the 20% limit and *δ* and $\sigma^{2}$ represent the expected value and variance of *d*, respectively. This inequality may be approximated by δ+2.5σ<λ indicating that the power is sufficient with *δ* = 5% and *σ* = 6%, for example. To fulfil the sample size recommended by Bland and Altman (i.e., ≥ 100 pairs of values), we plan to enrol up to 130 patients in this study.

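### The primary test's normal critical value gives a type I error of up to about 7% at 100 pairs, not 5%, when the true bias is about 2% or more

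*Protocol article*

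**What the plan says.** The Statistical methods section of the protocol article gives the confirmatory rule. The null hypothesis is |δ| + 2σ > λ, "where λ=20% for the outcome measure". The statistic is Z = (|d̄| + 2s_d − λ)/√(3s_d²/n). On the boundary it "is asymptotically normal. Therefore, the null hypothesis is rejected if" it is "below the 0.05 quantile of the normal distribution". The formula is printed there with a ± sign; I read it with a plus sign, as it appears under Interim analyses and stopping guidelines.

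The Sample size section uses the same approximation: "The standard error of the 95% limits of agreement is approximately" √(3s_d²/n). Its power condition has the threshold −2.486 and is called met at δ = 5% and σ = 6%. On numbers, "Bland and Altman recommend a sample size of 100", and "we plan to enrol up to 130 patients in this study".

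The Primary outcome measure section words success differently: the limits of agreement and their 95% confidence intervals must lie within 20%.

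**The concern.** The estimated s_d enters Z twice. When it is low by chance, the numerator becomes more negative and the standard error shrinks with it. Z is therefore skewed to the left, and a standard normal quantile is too lenient in the tail that leads to rejection. The error is one-directional: it favours declaring the device acceptable. Because the null hypothesis is that agreement is inadequate, the type I error here is the probability of accepting a device whose limits reach or exceed 20%.

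**Working it through.** **Inputs from the protocol article.** One-sided α = 0.05 with a normal quantile, and λ = 20% (Statistical methods). Standard error √(3s_d²/n), n = 100 pairs, up to 130 enrolled, δ = 5%, σ = 6% (Sample size). Assumption: the d_i are independent and normally distributed.

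**The plan's own figures reproduce.**
- 1.645 + 0.842 = 2.486, up to rounding.
- 1.96 × √(3/100) = 0.339, the stated 0.34 s_d.
- At n = 100, (5 + 12 − 20)/√(3 × 36/100) = −3/1.039 = −2.887, which is below −2.486. Normal-approximation power is Φ(2.887 − 1.645) = 89.3%.

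**The rule as a multiplier of s_d.** Z < −1.645 is the same as |d̄| + k·s_d < 20%, with k = 2 + 1.645·√(3/n).
- n = 100: k = 2 + 1.645 × 0.1732 = 2.285
- n = 130: k = 2 + 1.645 × 0.1519 = 2.250

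**Exact type I error.** When δ is clearly above zero, |d̄| = d̄ in practice. Then √n(λ − d̄)/s_d is noncentral t with n − 1 degrees of freedom and noncentrality √n(λ − δ)/σ. On the boundary (λ − δ)/σ = 2, so the error is P{t(n − 1; 2√n) > k√n}.
- n = 100: P{t(99; 20) > 22.85} = 7.03%
- n = 130: 6.75%

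Near δ = 0 the absolute value matters, so the probability was integrated over d̄ and s_d, with σ = (20 − δ)/2:

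| True bias δ | n = 100 | n = 130 |
|---|---|---|
| 0% | 1.6% | 1.5% |
| 0.5% | 3.2% | 3.2% |
| 1% | 4.9% | 5.0% |
| 2% | 6.8% | 6.7% |
| 3% and above | 7.0% | 6.8% |

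Simulation with 1,000,000 replicates per setting agrees (n = 100, δ = 5%: 7.03%). Treating the futility stop at 20 patients as binding changes little (n = 100, δ = 5%: 6.96%).

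**Cause and speed of convergence.** With the true σ in the denominator, the error at n = 100 and δ = 5% is about 5.2%, so the estimated denominator explains most of the excess. The maximum is still 6.4% at n = 200 and 5.6% at n = 1000.

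**Exact critical value.** k = t(0.95; n − 1, ncp 2√n)/√n gives 2.320 at n = 100 (Z < −1.849) and 2.277 at n = 130 (Z < −1.820). At δ = 5%, σ = 6% the noncentrality is √n × 15/6 = 2.5√n:

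| Rule | k, n = 100 | Max. error | Power | k, n = 130 | Max. error | Power |
|---|---|---|---|---|---|---|
| Current test (1.645) | 2.285 | 7.0% | 87.6% | 2.250 | 6.8% | 93.7% |
| Exact 5% | 2.320 | 5.0% | 83.2% | 2.277 | 5.0% | 91.3% |
| 95% CI rule (1.96) | 2.339 | 4.1% | 80.5% | 2.298 | 3.9% | 89.1% |
| Exact one-sided 2.5% | 2.387 | 2.5% | 72.8% | 2.334 | 2.5% | 84.3% |

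**Non-normal differences (illustration only).** With d_i from a t distribution on 5 df, scaled so that δ = 5% and σ = 7.5%, n = 100, simulation gives a false-success rate of about 17% under the current rule and still about 13.5% with k = 2.320.

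**The case against.** The strongest reply is that nothing stated is false. The article calls the normal distribution asymptotic and the standard error approximate, and both belong to the Bland-Altman method it cites. That stands as a description, but the section goes on to fix the 0.05 normal quantile as the decision rule at about 100 pairs, and there the rule does not deliver its stated level. The unseen analysis plan may refine the interval construction or sensitivity analyses, but it does not alter the rule printed here.

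A second reply is that the practical effect is small, and this largely stands. The change in k is 0.035 s_d, about 0.26 percentage points at σ = 7.5%. The excess also concerns devices close to the limit: with δ = 5% and n = 100, the current rule accepts 5.3% of the time at a true |δ| + 2σ of 20.2%, and 1.6% at 21%.

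Third, the confidence interval rule under Primary outcome measure, read with 1.96, stays below 5%. That is correct, so the 7% belongs only to the test under Statistical methods.

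Three stronger readings are tempting and not supported:
- That the error is 7% in general. It is a maximum over the null; near zero bias the test is conservative.
- That the confidence interval rule breaches a planned 2.5% level. The article states no such level; it would have to be inferred from the two-sided 95% interval.
- That the real error is about 17%. That rests on an assumed t distribution with 5 df, and the article says nothing about the distribution of the differences.

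**Conclusion.** The point holds in limited form. For normal differences, the test under Statistical methods has a true type I error of up to 7.0% at 100 pairs and 6.8% at 130, against a stated 5%: an excess of about 2 percentage points, or 40% in relative terms at n = 100 (7.03/5 = 1.41). It applies from a true bias of about 2% upwards, including the article's planning value of 5%. For bias up to about 1% the test holds its level. The result rests on normal, independent d_i and on reading the printed ± as plus.

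The planning conclusion survives the correction: power at the planning values stays above 80%. The two success rules remain to be reconciled, because they differ in both error rate and power.

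**What to change.** 1. Replace the normal quantile by the exact one: reject if |d̄| + k·s_d < 20%, with k = t(0.95; n − 1, ncp 2√n)/√n for the number of pairs actually analysed (2.320 at 100, 2.277 at 130). Print the statistic with a plus sign.
2. Restate power at δ = 5%, σ = 6% as 83% at 100 pairs and 91% at 130.
3. State which rule decides success, this test or the 95% confidence interval rule. If the latter is kept with 1.96, report its maximum false-success rate as 4.1% at 100 pairs and 3.9% at 130. If an exact one-sided 2.5% is wanted, use k = 2.387 and 2.334 and restate power as 73% and 84%; at 100 pairs that falls short of 80%.
4. Add a bootstrap confidence interval of the limits as a sensitivity analysis for non-normal differences, and keep this separate from the change of critical value.

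The first two items take one line of text and code and no extra patients. They can go into the statistical analysis plan, which the article says is to be authorised before the database is opened. At n = 100 the cost in power against the current rule is about 4 percentage points (87.6% to 83.2%).

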### Primary outcome measure

The primary outcome measure, referred to as the agreement at point of care, is defined as the level of agreement in blood glucose levels determined by the CGM and a BGA, assessed 8 h after the initial placement and calibration of the CGM.

The agreement for the *i*th patient will be quantified as the relative difference $d_{i}$ between readings ($y_{\mathrm{gi}}$) and measurement results ($y_{\mathrm{ri}}$), calculated as $d_{i}=\frac{2\left(y_{\mathrm{gi}}-y_{\mathrm{ri}}\right)}{y_{\mathrm{gi}}+y_{\mathrm{ri}}}$. Using the approach suggested by Bland and Altman [9,10] the limits of this agreement are set to $\bar{d}\pm 2s_{d}$, where $\bar{d}$ and $s_{d}$ are the empirical mean and the standard deviation of *d*_*i*_.

According to the guidelines for quality assurance in quantitative laboratory tests issued by the German Medical Association (GMA) [11,12], the measurement results from any device should not differ from an established standard by more than 15%. In this setting, however, the standard is not an unknown clinical value measured with a standard device but instead a prepared sample for which accuracy was achieved by titration or other methods. Unlike this method, the test–retest variance of the standard device contributes to the total error in our study. Moreover, the asymmetrical measure $\frac{1}{y_{0}}\sqrt{\frac{1}{n}{\left(y_{i}-\;y_{0}\right)}^{2}}$ is smaller than the measure $\left|\bar{d}\right|\pm 2s$ taken from the symmetrical limits of agreement under any but highly unlikely conditions. Thus $\bar{d}\pm 2s_{d}$ has been set to 20%, which is more conservative than the requirements imposed by the GMA. Therefore, the agreement at point-of-care is considered sufficient if the limits of agreement of the relative difference and their 95% confidence intervals (CIs) are within 20%.

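### The primary success criterion is fixed at two levels: 95% confidence intervals within 20%, and a one-sided 5% test

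*Protocol article*

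**What the plan says.** Four sections of the protocol article bear on the level of the primary criterion.

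- **Primary outcome measure.** Agreement is sufficient if "the limits of agreement of the relative difference and their 95% confidence intervals (CIs) are within 20" per cent.
- **Sample size.** For 100 pairs the recommended design is one "which gives a 95% CI of about" ±0.34 s_d. The power to reject is said to exceed 80% if (δ + 2σ - λ)/√(3σ²/n) is below -2.486. This is then shortened to δ + 2.5σ < λ, with δ = 5% and σ = 6% as the example.
- **Interim analyses and stopping guidelines.** The futility analysis uses θ = u(1-α) + u(1-β) and the bound 0.813 after 20 patients.
- **Statistical methods.** The null hypothesis |δ| + 2σ > λ is rejected if Z "is below the 0.05 quantile of the normal distribution". The numerator of Z is printed with ± before 2s_d. The interim section prints +.

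**The concern.** The interval rule and the test use the same estimate, the same standard error and the same 20% margin. They differ only in the critical value. If the 95% interval is two-sided, the interval rule is a one-sided 2.5% test, while Statistical methods specifies a one-sided 5% test. One data set can then meet one definition of success and miss the other, and the protocol gives no order of precedence. If the choice were left until the results were known, the favourable rule could be picked. The planning constants must also belong to one rule or the other, so the stated power and the futility bound need checking against both.

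**Working it through.** **Inputs.** λ = 20%, n = 100 pairs, δ = 5%, σ = 6% and SE = √(3s_d²/n), all from Sample size. The critical values come from Primary outcome measure and Statistical methods. Z is read with + and with denominator √(3s_d²/n), as Sample size and the null hypothesis require. At n = 100, √(3/100) = 0.1732.

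**1. Is the 95% interval two-sided?** 1.96 × 0.1732 = 0.339, which reproduces the stated 0.34. A one-sided 95% bound would give 1.645 × 0.1732 = 0.285. The stated figure is therefore two-sided.

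**2. The two rules at n = 100.** The limit nearer the margin decides, so |d̄| + 2s_d is what counts under both rules.

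- Interval rule: |d̄| + (2 + 1.96 × 0.1732)s_d = |d̄| + 2.339 s_d < 20%, that is Z < -1.96.
- Test: |d̄| + (2 + 1.645 × 0.1732)s_d = |d̄| + 2.285 s_d < 20%, that is Z < -1.645.

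**3. Data on which they disagree.** Take d̄ = 6.1% and s_d = 6%. Then SE = 6 × 0.1732 = 1.039 and Z = (6.1 + 12 - 20)/1.039 = -1.83.

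- Test: 18.1 + 1.645 × 1.039 = 19.81%, success.
- Interval rule: 18.1 + 1.96 × 1.039 = 20.14%, failure.

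At d̄ = 5% the rules disagree for s_d from about 6.41% to 6.56%. The disagreement runs one way only: the test can pass where the interval rule fails, never the reverse.

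**4. How often.** In 400,000 simulated trials with normal differences, δ = 5%, σ = 6% and n = 100, the test passed in 87.6% and the interval rule in 80.6%. They disagreed in 7.1%. On the null boundary (δ = 5%, σ = 7.5%, since 5 + 15 = 20) the rules passed in 7.1% and 4.2%.

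**5. The power constant.** z(0.95) + z(0.80) = 1.645 + 0.842 gives 2.486 to the protocol's rounding, so the stated constant is reproduced at one-sided 5%. At one-sided 2.5% it would be 1.960 + 0.842 = 2.802. Exactly at a ratio of -2.486, power is Φ(2.486 - 1.645) = 80.0% for the test and Φ(2.486 - 1.96) = 70% for the interval rule.

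**6. The shortcut and the worked example.** The multiplier of σ needed for 80% power at n = 100 is 2 + 2.486 × 0.1732 = 2.431 for the test and 2 + 2.802 × 0.1732 = 2.485 for the interval rule. The printed 2.5 covers both. The example lies on the edge of the shortcut (5 + 2.5 × 6 = 20). Its ratio is (5 + 12 - 20)/1.039 = -2.887, with these results:

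| Rule | Power, n = 100 | Power, n = 130 | Pairs for 80% power |
|---|---|---|---|
| Test, 0.05 quantile | Φ(2.887 - 1.645) = 89.3% | 95.0% | 75 |
| Two-sided 95% interval | Φ(2.887 - 1.96) = 82.3% | 90.8% | 95 |

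**7. The futility bound.** With information fraction 20/100 (an assumption that reproduces the printed figure) and conditional power 30%, the one-sided 5% level gives -1.645 + 0.8 × 2.486 + 0.524 × √0.8 = 0.813. The one-sided 2.5% level gives -1.960 + 0.8 × 2.802 + 0.524 × √0.8 = 0.750. This calculation serves here only to identify the α behind the printed bound.

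**The case against.** The strongest reply is that most of the plan is coherent at one-sided 5%. The 0.05 quantile, 2.486 and 0.813 all agree, and only the interval wording stands apart. Primary outcome measure never says two-sided, and the 0.34 s_d describes precision behind a cited recommendation of 100 pairs. It is true that two-sidedness is inferred. The inference is still sound: the Sample size section says that the limits with their 95% intervals "will be compared with a prespecified, clinically acceptable relative difference [9] of 20" per cent, and the only 95% interval it quantifies is two-sided. What stands of the reply is that aligning the interval to the test may be the smaller change.

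A second reply is that the statistical analysis plan will settle the details. That plan is not shown and may do so. But this is not an omitted detail: two rules are stated, and any later document can agree with only one of them.

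A reader might also infer that the study is underpowered for its own success definition. The documents do not support this. The 70% applies only exactly at -2.486, while the shortcut and the example keep more than 80% under both rules at 100 pairs.

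Nor does the ± in the printed Z make the test vacuous. The null hypothesis in the same sentence and the interim formula both show that + is meant, so it is a notation slip.

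**Conclusion.** The contradiction is real and concerns the primary decision threshold. Its reach is limited. The disagreement is confined to -1.96 ≤ Z < -1.645, always in the direction of the test passing and the interval rule failing, and arises in about 7% of trials at the planning values. The nominal false-success rates are 5% and 2.5%. It would be too strong to say that the actual rate doubles: in the simulated boundary case the rates were 7.1% and 4.2%, a ratio of about 1.7.

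Of the planning figures, 2.486 and 0.813 are tied to the 5% rule. The planned sample size stands under either rule, provided the example's δ and σ hold and at least 95 pairs can be analysed. The protocol aims for at least 100.

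The conclusion rests on the two-sided reading of the 95% interval, on the protocol's normal approximation and, for the simulated rates, on normally distributed differences.

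**What to change.** Choose one level before the data are seen and state it in Primary outcome measure, Sample size, Interim analyses and stopping guidelines, and Statistical methods. Either choice is coherent:

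- **(a) One-sided 5%.** In Primary outcome measure, specify two-sided 90% intervals (one-sided 95% bounds). The 0.05 quantile, 2.486 and the α behind 0.813 stay. This changes the fewest figures.
- **(b) One-sided 2.5%.** Keep the 95% intervals and say that they are two-sided. Use the 0.025 quantile in Statistical methods and 2.80 in Sample size, and recompute the futility bound and the probabilities quoted with it. The calculation that gives 0.813 then gives 0.750. The power of the example at 100 pairs is then 82%, where one-sided 5% would give 89%.

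Under both options, print + in place of ± in the Z formula in Statistical methods, as an editorial correction. The cost is wording under (a), and wording plus a few constants under (b). The number of patients does not change.

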## Discussion

Hyperglycaemia, insulin resistance [2,3], and metabolic acidosis often occur in critically ill patients. Several authors have independently, but consistently reported that intensive insulin therapy reduces morbidity in all patients and mortality in some patients [2,3,22-24]. Of particular interest in terms of the number of patients enrolled and methodological quality, are two trials conducted by Van Den Berghe et al. [2,3]. In 2001 Van Den Berghe et al. reported on a trial terminated after 1548 patients [2], as the fourth interim analysis revealed that conventional treatment (insulin infusion if the blood glucose level was > 215 mg/dL to maintain blood glucose levels between 180 and 200 mg/dL) was inferior to intensified insulin therapy (maintenance of blood glucose levels between 80 and 110 mg/dL). Morbidity and mortality were significantly reduced but intensified insulin therapy reduced morning blood glucose levels at the expense of a substantially greater risk of hypoglycaemia. In 2006, Van Den Berghe et al. reported on a subsequent trial enrolling 1200 patients [3]. Morbidity was significantly reduced but mortality was not. Again, intensive insulin therapy reduced morning blood glucose levels at the expense of a significantly greater risk of hypoglycaemia. However, results of the VISEP study at least partly conflicted with those of the studies by Van Den Berghe et al. The VISEP study was initiated to investigate the effects of intensive insulin therapy in a two-by-two factorial design [22]. The intensified insulin regimen was virtually identical to that described by Van Den Berghe et al. Blood samples used to adjust the continuous infusion of insulin were taken at least every 4 h. The trial was partially terminated for safety reasons after enrolling 488 patients. Intensive insulin therapy significantly reduced the mean morning blood glucose levels. However, this reduction did not result in any difference in outcome but did increase the risk of severe hypoglycaemia and the rate of serious adverse events. Considering these results, the devices currently in clinical use are not sufficient to detect impending hypoglycaemia [25]. Continuous assessment of blood glucose levels has several advantages. First, it shows the actual blood glucose levels at any time with no gaps between scheduled sampling and assessment times. Accordingly, it may detect hypoglycaemic and hyperglycaemic events that might have been missed. It may even help to predict these events in advance based on the trends in values. Therefore, the CGM would facilitate the use of intensive insulin therapy for seriously ill patients, and may improve the morbidity and mortality of these patients. the CGM may also be used within an artificial pancreas by forming a control loop, which consists of a tool for continuous measurement of blood glucose levels, an insulin pump, and an intravenous source of glucose for rescue [26]. However, no devices are currently available to continuously assess blood glucose levels in critically ill patients. Several attempts have been made to develop a device to continuously measure blood glucose levels within an intensive care setting [27,28] or to use the devices that were originally designed for diabetes management, as several of these devices are already available [25,29,30]. However, none of these devices were successful in intensive care settings. The results of this study and the introduction of the CGM may resolve this limitation by confirming the ability of the CGM to continuously measure blood glucose levels in intensive care settings.
